### 3.3.3 Decision Rule

This trial is designed to address a single primary outcome. Non-inferiority is claimed if the primary null hypothesis is rejected on the significance level (alpha) of 0.025 (one-sided). That is, if the upper-limit of the two-sided 95% confidence interval for the treatment difference is less than 7%.

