Because the lack of comparable non-inferiority designed trials with the same primary outcome measurement (sUTI) it is chosen to look at non-inferiority trials with a primary outcome measurement of (treatment of) sUTI. All these trials handled a non-inferiority margin of 10% (18) (19-22), and two trials even 15% (23, 24). The head researchers and clinicians of the departments of urology and medical microbiology agreed on the 11% margin to be clinical acceptable.

In addition, we encountered the unique challenge of conducting a study with a significantly extended follow-up period of one year, in contrast to the previous studies used in the sample size calculation above, with a shorter follow-up of 2-4 months. Recognizing the impact of time on the occurrence of urinary tract infections (UTIs) and the need to account for this extended observation period, we also performed a sample size calculation that considered the monthly UTI rates observed by Vapnek et al. (25) This calculation factored in not only the proportion of UTIs but also the temporal aspect, recognizing that the incidence of UTIs may vary over time. Vapnek et al. found that single-use catheters had

an average of 0.13 UTIs per month (SD 0.18) and multiple-use catheters had an average of 0.14 UTIs per month (SD 0.21) per patient (25). We applied the same power of 0.80 and an one-sided alpha of 0.025. A non-inferiority margin of 7% has been determined based on 50% of the means following the recommendation of Althunian et al. (15) We used the most conservative standard deviation of 0.21 and the sample size calculation was performed using the formula developed by Julious:  $n = f(\alpha, \beta) \times 2 \times \sigma^2 / d^2$  (26). This calculation led to a requirement of 152 effective cases in each group. Anticipating a dropout rate of 20%, this figure was divided by 0.80, resulting in a total sample size of 382 participants (191 in each group). Since the sample size of 382 is almost equal to our sample size that does not correct for time (n=386), we will include 386 participants to account for both methods.

Sample size: 386 patients.

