## 10. STATISTICAL ANALYSIS

### 10.1 Primary study parameters

For analysis of the results, the groups will be stratified for gender and the female patient group will be balanced for pre- and post-menopausal. Data analysis will be performed using SPSS. The primary analysis will be to assess difference between the intervention and the control groups in the sUTI rate and other adverse effects. Descriptive statistics will be used to describe baseline characteristics of participating patients in both groups. Binomial or categorical outcome measures will be analyzed using Chi-square tests and quantitative outcome variables by t-tests or Mann-Whitney U tests. Two-sided p values are calculated.

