## 6.1.2 Primary Analysis

For the primary outcome, the incidence rate in each group is the total number of UTIs divided by the total follow-up time, reported with 95% confidence intervals calculated using bootstrap procedure. The absolute difference between groups will be calculated and reported with a 95% bootstrap confidence interval. Non-inferiority will be concluded if the upper limit of the CI is below the non-inferiority margin of 7%. The incidence rate ratio (IRR) with a 95% CI will be estimated in both arms using a poisson or negative binomial regression model (in case there is overdispersion of the data). All analyses will be conducted using R version 4.2.1 (R Foundation for Statistical Analysis, Vienna, Austria).

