# STATISTICAL ANALYSIS PLAN for COMPaRE-trial

---

noninferiority margin to 14%. As this was deemed inappropriate, we opted to maintain the margin at 11%. The sample size is then calculated with:  $n = ((Z(1-\alpha) + Z(1-\beta))^2 [ps(1-ps) + pe(1-pe)]) / ((ps-pe-d)^2)$ , the formula developed by Blackwelder et al in 1982 (13), leading to 154 effective cases in each group. Anticipating a dropout of 20% (14), this must be divided by 80% and rounded upwards. This results in 2 times 193 participants, a total of 386. Because the lack of comparable non-inferiority designed trials with the same primary outcome measurement (sUTI) it is chosen to look at non-inferiority trials with a primary outcome measurement of (treatment of) sUTI. All these trials handled a non-inferiority margin of 10% (15-19), and two trials even 15% (20,21). The head researchers and clinicians of the departments of urology and medical microbiology agreed on the 11% margin to be clinically acceptable. In addition, we encountered the unique challenge of conducting a study with a significantly extended follow-up period of one year, in contrast to the previous studies used in the sample size calculation above, with a shorter follow-up of 2-4 months. Recognizing the impact of time on the occurrence of urinary tract infections (UTIs) and the need to account for this extended observation period, we also performed a sample size calculation that considered the monthly UTI rates observed by Vapnek et al. (22) his calculation factored in not only the proportion of UTIs but also the temporal aspect, recognizing that the incidence of UTIs may vary over time. Vapnek et al. found that single-use catheters had an average of 0.13 UTIs per month (SD 0.18) and multiple-use catheters had an average of 0.14 UTIs per month (SD 0.21) per patient (23). We applied the same power of 0.80 and an one-sided alpha of 0.025. A non-inferiority margin of 7% has been determined based on 50% of the means following the recommendation of Althunian et al. (24) We used the most conservative standard deviation of 0.21 and the sample size calculation was performed using the formula developed by Julious:  $n = f(\alpha, \beta) \times 2 \times \sigma^2 / d^2$  (245). This calculation led to a requirement of 152 effective cases in each group. Anticipating a dropout rate of 20%, this figure was divided by 0.80, resulting in a total sample size of 382 participants (191 in each group). Since the sample size of 382 is almost equal to our sample size that does not correct for time ( $n=386$ ), we will include 386 participants to account for both methods.

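### Protocol 10.1 tests the primary outcome for a difference, not for non-inferiority, and the SAP's 7% margin is in the wrong unit and is a rounding of the value behind the stated sample size

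*Combined protocol and SAP*

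**What the plan says.** **Protocol 10.1 (primary study parameters)** describes the primary analysis as an assessment of the difference between groups in the sUTI rate and other adverse effects. The methods given are: "Binomial or categorical outcome measures will be analyzed using Chi-square tests and quantitative outcome variables by t-tests or Mann-Whitney U tests". P values are two-sided. The section mentions no margin and no confidence-interval criterion.

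**SAP 3.3.3** claims non-inferiority "if the upper-limit of the two-sided 95% confidence interval for the treatment difference is less than 7" percent. SAP 6.1.2 repeats it: "Non-inferiority will be concluded if the upper limit of the CI is below the non-inferiority margin of 7" percent. SAP 3.3.1 states its hypotheses on the monthly incidence of UTIs with the same 7%. SAP 6.1.2 also says that the treatment difference is absolute, with each group's rate being total UTIs over total follow-up time.

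**Protocol 4.4** (repeated in SAP 6.3) gives the origin of the figure: "A non-inferiority margin of 7% has been determined based on 50% of the means". The means are 0.13 (single use) and 0.14 (multiple use) UTIs per month, taken from an earlier randomised catheter comparison. With SD 0.21, "This calculation led to a requirement of 152 effective cases in each group".

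The same sections carry a second margin, for the proportion of patients with an sUTI. The lead researchers and clinicians "agreed on the 11% margin to be clinical acceptable". No such agreement is recorded for the rate margin.

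**The concern.** Three things bear on how success is decided.

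- The protocol and the SAP prescribe different primary analyses. A test of difference that fails to reach significance shows only that no difference was detected. It does not bound the excess of infections with reusable catheters, which is the trial's question.
- The SAP's threshold is a percentage, but a difference in UTIs per patient-month is not one. A clinician or ethics committee reading 7% cannot see how many extra infections are being accepted.
- The sample size and the decision rule use slightly different values of the margin, and the value used for sizing is not printed anywhere.

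The trial is open-label (Protocol 8.2), so there is added reason to have one explicit success rule, with a clinically accepted margin, before the data are locked.

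**Working it through.** **Inputs** (Protocol 4.4 and SAP 6.3): rates 0.13 and 0.14 UTIs per month; SD 0.21; power 0.80; one-sided alpha 0.025; true difference taken as zero, since the printed formula contains no such term. The formula is n = f(α,β) × 2σ²/d², where f = (1.960 + 0.842)² = 7.849.

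**1. The plan's own figure.** Half the mean of the two rates is 0.5 × (0.13 + 0.14)/2 = 0.0675.

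- d = 0.0675: n = 7.849 × 2 × 0.21² / 0.0675² = 151.9, so 152. This reproduces the stated number.
- d = 0.07: n = 7.849 × 2 × 0.21² / 0.07² = 141.3, so 142. This does not.

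Solving back from n = 152 gives d = 0.0675. Other variants at d = 0.07 also miss 152: a t-based calculation gives 143, one-sided alpha 0.05 gives 112, alpha 0.0125 gives 172, and a true difference of 0.01 gives 193. The sizing therefore used 0.0675 and the decision rule uses it rounded to 0.07.

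**2. What the margin means.** 0.07 × 12 = 0.84 extra UTIs per patient-year, and 0.07/0.13 = 54% above the assumed control rate. For 0.0675 the figures are 0.81 per patient-year and 52%.

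**3. What the rounding does to power.** At 152 per arm the standard error is 0.21 × √(2/152) = 0.0241, and power is Φ(d/0.0241 − 1.96) at zero true difference.

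| Margin (UTIs per patient-month) | Power at 152 per arm | Largest observed difference that passes |
|---|---|---|
| 0.0675 | 80.0% | 0.0675 − 0.0472 = 0.0203 |
| 0.07 | 82.8% | 0.07 − 0.0472 = 0.0228 |

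Here 0.0472 is 1.96 × 0.0241.

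**4. How Protocol 10.1 and the SAP can disagree.** On the same planning values, a two-sided 5% test of difference is non-significant for any observed excess below 0.0472. The SAP rule at 0.07 passes only below 0.0228. An observed excess between 0.0228 and 0.0472 would be reported as no significant difference under Protocol 10.1 while failing non-inferiority under the SAP.

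**5. Error rate.** Against the declared null at 0.07, the confidence-interval rule has nominal one-sided error 2.5%. If 0.0675 were the intended margin, testing against 0.07 would give Φ(0.0025/0.0241 − 1.96) = 3.2%.

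**The case against.** The strongest reply is that there is one rule and it is clear enough. Three parts of this stand.

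- A reader might infer that the SAP holds several success rules. It does not: 3.3.1, 3.3.3 and 6.1.2 all use 7%, and the last two state the same confidence-interval criterion.
- A reader might take 7% as relative to the control rate, which would be 0.07 × 0.13 = 0.0091 per month. The documents rule this out. SAP 6.1.2 defines an absolute difference, the margin is derived as half of the mean rates, and the relative reading would need about 8,360 patients per arm.
- A reader might infer that the protocol has no margin. Protocol 4.4 states both 7% and 11%; it is the analysis section that omits them.

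It can also be said that the list of tests in Protocol 10.1 is generic, in a section that also covers other adverse effects, and that the SAP presents itself as a supplement to the protocol (SAP 2.1). That softens the conflict but does not remove it. The list stands under the primary study parameters, Chapter 10 offers no other method for the primary outcome, and the available text of the SAP does not say that it replaces Section 10.1.

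**Conclusion.** The concern holds, mainly as a conflict between protocol and SAP. Protocol 10.1 contains no analysis that could establish non-inferiority, and the SAP does. This is what most needs correcting.

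The unit is wrong as printed, but its meaning can be recovered as about 0.07 UTIs per patient-month. The gap between 0.07 and 0.0675 is rounding: 0.0025 per month, or 0.03 per patient-year. It would change the conclusion only if the upper confidence limit fell between the two values.

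Two stronger conclusions are not supported. The rounding does not leave the trial short of patients, because power against the declared margin is above 80% at 152 per arm. Nor is the type I error simply inflated: the 3.2% applies only if 0.0675 is the intended margin, and the plan declares its null at 7%.

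The power figures assume SD 0.21, a normal approximation in place of the planned bootstrap, and zero true difference. If the true difference were the 0.01 seen between the cited rates, power at 152 per arm would be 70.2% against 0.07 or 66.5% against 0.0675.

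The absence of recorded clinical agreement for the rate margin is a gap in the record. It does not show that clinicians would reject that margin.

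**What to change.** 1. In Protocol 10.1, replace the difference tests for the primary outcome with the SAP rule: reusable catheters are non-inferior if the upper limit of the two-sided 95% confidence interval for the absolute rate difference, reusable minus single use, is below the margin.
2. State one margin in UTIs per patient-month in Protocol 4.4 and 10.1 and in SAP 3.3.1, 3.3.3, 6.1.2 and 6.3. Leaving 7% in the sample-size sections would create a new mismatch. Either choice gives one rule:
   - **0.0675**, which matches the derivation and the 152. It is a slightly stricter threshold than the one printed and costs about 2.8 power points at zero difference (82.8% to 80.0% at 152 per arm).
   - **0.07**, with the stated sample size corrected to 142 per arm. After 20% dropout this is 142/0.80 = 177.5, so 178 per arm and 356 in total. The target of 386 comes from the proportion calculation and need not change, but the remark that the two totals are nearly equal would have to.
3. Before database lock, have the clinicians who accepted the 11% proportion margin record whether they accept the chosen rate margin, expressed per patient-year (0.81 or 0.84).

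The cost is a protocol amendment and SAP wording. No new data or extra patients are needed.

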## 3.4 Timing of Outcome Assessments

For all clinically planned measures, visits should occur within a window of the scheduled visit. The target day and visits window is defined in the protocol as:

| Label                 | Target Week            | Definition (Week window) |
|-----------------------|------------------------|--------------------------|
| KC0, baseline (Day 0) | Week 0 (randomisation) | Day 0                    |
| TC1                   | Week 1                 | Target week +/- 3 weeks  |
| KC2                   | Week 6                 | Target week +/- 3 weeks  |
| TC2                   | Week 12                | Target week +/- 3 weeks  |
| TC3                   | Week 18                | Target week +/- 3 weeks  |
| KC3                   | Week 26                | Target week +/- 3 weeks  |

## STATISTICAL ANALYSIS PLAN for COMPaRE-trial

---

|                        |         |                         |
|------------------------|---------|-------------------------|
| TC4                    | Week 34 | Target week +/- 3 weeks |
| TC5                    | Week 42 | Target week +/- 3 weeks |
| KC4, last study visit* | Week 52 | Target week +/- 3 weeks |

\*The last study visit is defined as the visit following the last visit with randomised treatment, and where there is a study end statement.

### 3.5 Statistical Interim Analyses and Stopping Guidance

There will be no interim analyses in this trial.

### 3.6 Timing of Main Analysis

The main analysis is planned when all patients have concluded  $52 \pm 4$  weeks of treatment, all data up to 52 weeks have been entered, verified and validated and the primary database has been locked.

## 4 Trial Population

### 4.1 Screening Data, Eligibility and Recruitment

A CONSORT flow diagram (appendix A) will be used to summarise the number of patients who were:

- assessed for eligibility at screening
- eligible at screening
- ineligible at screening\*
- eligible and randomised
- received the randomised allocation
- lost to follow-up\*
- discontinued the intervention\*
- randomised and included in the primary analysis
- randomised and excluded in the primary analysis\*

\*reasons will be provided.

### 4.2 Baseline Patient Characteristics

The patient demographics and baseline characteristics to be summarised include age in years, BMI, sex, menopausal status, race, comorbidities (COPD, DM2, hypertension, cardiovascular disease), underlying cause of catheterization (e.g., NLUTD vs non-NLUTD), spontaneous miction, hand function, years of CIC experience, CIC frequency, Antibiotic prophylaxis, bladder irrigation, intradetrusor botulinum toxin A, self-reported UTI in previous 6 months before trial.

## STATISTICAL ANALYSIS PLAN for COMPaRE-trial

---

Patient demographics and baseline characteristics will be summarised by randomised treatment arm and overall using descriptive statistics (N, mean, standard deviation, median, 25/75 percentiles, minimum, and maximum) for continuous variables, and number and percentages of patients for categorical variables. There will be no statistical analysis of treatment difference. Any clinical important imbalance between the treatment groups will be noted.

### 4.3 Withdrawal/Follow-up

The status of eligible and randomised patients during the trial will be presented in a flowchart according to treatment group.

- completed intervention
- withdrew consent
- lost to follow-up

Time from randomisation to treatment discontinuation and time from randomisation to withdrawal/lost of follow-up will be presented in a table. Information on the number of withdrawals, reasons for withdrawal, and number included in the analysis will be provided.

### 4.4 Adherence and Protocol Deviations

#### 4.4.1 Adherence to Allocated Treatment

Adherence is assessed based on the percentage of patients in the intervention arm who use single-use catheters within the acceptable limit. In this study, patients in the intervention arm are allowed to use a maximum of 20% single-use catheters. If the percentage exceeds 20% persistently, the patient will be considered non-compliant.

Patients in the single-use catheter arm are required to use only single-use catheters and may not reuse them.

Data summarizing the proportions of patients complying with the treatment regimen according to protocol will be presented by treatment arm.

#### 4.4.2 Protocol Deviations

The following protocol deviations, which impact the statistical analyses, will result in exclusion from the Per-Protocol Set (PP):

- Entering the trial when the eligibility criteria should have prevented trial entry
- Discontinuation of intervention prior to 52 weeks
- Use of single-use catheters in more than 20% of catheterizations in the intervention arm
- A new onset exclusion criterium.

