
disposable (single-use) catheters. (8, 12). In the Netherlands the use of single-use catheters for CIC is almost 100%. In contrast, the use of reusable catheters in countries outside Europe is much higher, possibly due to restraints in healthcare budget (12).

Possible advantages of reusable catheters include health care cost efficiency. Potential savings are calculated globally (see Appendix 'Potential Savings') if 50% of all patients in the Netherlands start using the reusable catheter. The costs of the single use catheters vary widely. For this calculation two prices were used (1.03 and 1.70 euro's per catheter). The potential savings vary from 13.184.437,50 to 23.272.125,00 euro's a year in the Netherlands. Other possible advantages of reusable catheters include environmental advantages. The majority of patients feels a growing responsibility for environmental consequences of the use of catheters and keeping healthcare affordable, as do patients that are on CIC.

The potential environmental waste savings are also calculated globally (see Appendix 'Potential environmental waste savings') if 50% of all patients in the Netherlands start using a reusable catheter. The potential average environmental waste savings is estimated on 371.480 kg/year in the Netherlands, which is a possible reduction of 48,7% of all waste generated by single use catheters in the Netherlands. This calculation is based on the study of Sun et al, which investigated the environmental aspects of single use catheters in the United states (13).

The last possible advantages of the reusable catheters, but equally important, include more patient choice and reducing fear of running out of catheters. Several healthcare insurances, provide up to four catheters a day, which is often not sufficient for the needs of all patients. This introduces potential stress for the patients and does not stimulate the health of the individual patient. Also, it is clear that storage of large amounts of catheters, or travelling for vacation with a stock of needed catheters, is not ideal for patients and gives fear of running out of catheters.

Our group has found that a CE-certified Japanese manufacturer designed a reusable catheter. This catheter will be used to introduce the reusable catheter in Europe through this study.

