| Week 12          | Telephone call           | The use of both types of catheters will be evaluated, patients will be asked for adverse events through standardized questions in Gemstracker/LimeSurvey and possible risen questions will be answered.                                                                                                                                                                                                                                                |                                                                                                                                                                                                                     |
| Week 18          | Telephone call           | The use of both types of catheters will be evaluated, patients will be asked for adverse events through standardized questions in Gemstracker/LimeSurvey and possible risen questions will be answered.                                                                                                                                                                                                                                                |                                                                                                                                                                                                                     |

|                          |                  |                                                                                                                                                                                                                                                                                                                                          |                                                                                                                                                                                                                                                                      |

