#### **6.5 Description and justification of route of administration and dosage**

All patients will CIC 4-6 times a day, depending on their needs, this will not differ between the intervention and the control group. Patients in the intervention group will use the

reusable catheter and the control group will remain using the single use catheter. All patients are able to catheterize themselves through the urethra.

The reusable catheters are fabricated by Create Medic, a Japanese medical manufacturer with a broad experience in urological products. The reusable catheters are made by the CE-marked manufacturer and registered in the Z-index, so it will be reimbursed through the Dutch health insurances. An independent retailer will provide the catheters to the suppliers in the Netherlands. When a patient decides to withdraw from this trial, they can return the given catheters to the supplier.

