## 4.5 Analysis Populations

The Enrolled set will include all patients who have provided informed consent and have been included into the study data base.

The intention-to-treat (ITT) analysis set will include all patients randomly assigned to a treatment group, who started with the treatment, regardless of whether they completed the treatment or adhered to the protocol.

The modified intention-to-treat (mITT) analysis set will include all patients who were randomly assigned to a treatment group with at least 6 weeks of follow-up data (i.e., those who attended the first clinical follow-up visit).

The Per Protocol (PP) Analysis Set will include all randomised patients meeting the study eligibility criteria who completed the 52 weeks follow-up. (i.e., those who attended the final study visit).

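### The per-protocol set has no exclusion for control patients who reuse catheters, although the SAP forbids such reuse; if reuse raises the UTI rate, the per-protocol estimate is pulled towards non-inferiority.

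*Combined protocol and SAP*

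**What the plan says.** SAP 4.4.1 sets an adherence rule for each arm. For the reusable arm there is a tolerance: "patients in the intervention arm are allowed to use a maximum of 20% single-use catheters". For the control arm there is none: "Patients in the single-use catheter arm are required to use only single-use catheters and may not reuse them". The section also promises a summary of compliance by arm.

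SAP 4.4.2 lists four deviations that remove a patient from the PP set. Two concern eligibility (ineligible at entry, or a new exclusion criterion later). One is "Discontinuation of intervention prior to 52 weeks". The fourth is the only crossover item: "Use of single-use catheters in more than 20% of catheterizations in the intervention arm".

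SAP 4.5 defines the set differently: "The Per Protocol (PP) Analysis Set will include all randomised patients meeting the study eligibility criteria who completed the 52 weeks follow-up". It mentions no crossover in either direction and does not refer to 4.4.2.

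SAP 6.1.2 describes the non-inferiority test without naming an analysis set. SAP 6.1.1 refers to a full analysis set that 4.5 does not define. Nowhere is the PP set called primary, co-primary or supportive.

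On data collection, the Protocol section 3 schedule says of several calls: "The use of both types of catheters will be evaluated".

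**The concern.** The stricter of the two adherence rules has no consequence for the analysis. A reusable-arm patient with 25% single-use is removed under 4.4.2. A control patient with 25% reuse, against a zero allowance, stays in.

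In a superiority trial such contamination usually works against the claim. In a non-inferiority trial it can work for it: if reuse causes infections, reuse among controls raises the control rate and narrows the gap to the reusable arm. A PP set is normally where a reader looks to see whether crossover explains a finding of no difference. Here one of the two directions of crossover is left in.

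The protocol gives some reason to think that control reuse could occur. Section 1 says several insurers "provide up to four catheters a day, which is often not sufficient for the needs of all patients", while section 6.5 states "All patients will CIC 4-6 times a day, depending on their needs". The trial is also unblinded (Protocol 8.2).

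**Working it through.** **Which control patients does the plan exclude?**

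1. Under 4.4.2, a control patient who partly reuses is eligible, has no new exclusion criterion, has not stopped the allocated regimen, and is not in the intervention arm. No item applies.
2. Under 4.5, the same patient is eligible and attends week 52, so is included.
3. Both definitions therefore keep this patient. They also disagree with each other: 4.5 omits even the intervention-arm crossover rule.

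**The plan's own figure.** Inputs from Protocol 4.4 and SAP 6.3: SD 0.21, one-sided alpha 0.025, power 0.80, rates 0.13 and 0.14 UTIs per month, margin 50% of their mean.

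- Margin = 0.5 × (0.13 + 0.14)/2 = 0.0675, printed as 7%.
- n = 2 × (1.960 + 0.842)² × 0.21² / 0.0675² gives 152 per arm, which matches. The printed 0.07 would give 142.
- 152/0.80 = 190, against the stated 191.

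These small differences do not affect the point. I use 152 per arm and the 0.07 decision limit of SAP 3.3.3.

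**Effect of control reuse.** Let c be the share of control-arm exposure that is reuse, and D the true difference in UTIs per month. Assume that risk is proportional to the share of reuse and that a reused disposable carries the same risk as the trial's reusable catheter. The control rate then rises by cD, and the PP difference becomes D(1 − c).

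- SE = 0.21 × √(2/152) = 0.0241.
- Non-inferiority needs the upper 95% limit below 0.07, so the estimate must lie below about 0.07 − 1.96 × 0.0241 = 0.023.
- P(claim) = Φ((0.07 − D(1 − c))/SE − 1.96), a normal approximation to the planned bootstrap interval.

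The values of c are assumptions.

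| c | Expected difference if D = 0.07 | P(claim), D = 0.07 | P(claim), D = 0.01 | P(claim), D = −0.02 |
|---|---|---|---|---|
| 0% | 0.070 | 2.5% | 70.2% | 96.2% |
| 5% | 0.0665 | 3.5% | 70.9% | 95.9% |
| 10% | 0.063 | 4.75% | 71.7% | 95.5% |
| 20% | 0.056 | 8.4% | 73.0% | 94.6% |
| 30% | 0.049 | 13.8% | 74.4% | 93.7% |

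Worked line, c = 10%, D = 0.07: (0.07 − 0.063)/0.0241 − 1.96 = −1.67, and Φ(−1.67) ≈ 0.0475.

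At D = 0.07 every claim is false, so that column is the error rate. D = 0.01 is the difference between the two planning rates (0.14 − 0.13). D = −0.02 is an assumed case in which reuse is protective; there the shift is slightly away from the claim.

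**The case against.** **Already covered?** SAP 4.4.1 promises compliance by arm, so breaches of the control rule should be visible. That is a table; it excludes nobody and does not say how control reuse is measured. The item on discontinuation could be read to cover a control patient who abandons single-use completely. A reader should therefore not infer that reuse throughout the year certainly stays in the PP set. Partial reuse, however, is not covered on any reading.

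**Does it bias the trial's conclusion?** A reader might infer so, but the documents do not support that. They give the PP set no role in the non-inferiority decision. What can be said is that the PP estimate itself is affected.

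**How common is control reuse?** A patient needing six catheterisations with four catheters supplied would be two short, or 33%. It is tempting to carry that over to the whole arm. But it describes one patient at the top of the range, and the protocol links short supply to stress and fear of running out, not to reuse. SAP 2.1 gives an average of four catheters a day (although its 1,825 a year implies five), and Protocol section 1 puts single-use practice in the Netherlands at almost 100%. No reuse rate is documented.

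**Could the dilution be larger?** One could add the permitted 20% single-use in the reusable arm, so that with 33% control reuse only 47% of the true difference would remain. That allowance is a separate design choice and would dilute the difference even with no control reuse. Nor does an observed difference of 0.07 pass the rule, which concerns the upper confidence limit.

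**Direction.** The pull towards non-inferiority is conditional on reuse raising UTIs. Equal risk from a reused disposable and a hypochlorite-stored reusable catheter is also an assumption. Both objections stand as limits on size; neither removes the gap.

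**Conclusion.** The point holds in a limited form. The SAP forbids control-arm reuse, gives the breach no consequence in 4.4.2, and has no crossover criterion at all in 4.5. Following the plan as written leaves partly reusing controls in the PP set. This is more than a missing detail, because the listed exclusions do not match the SAP's own adherence rule.

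The direction is towards non-inferiority if reuse raises the UTI rate. The size cannot be known from the documents. At the margin, control reuse of 10% would nearly double the nominal 2.5% error, and 20% would more than triple it. At a true difference of 0.01 the chance of a claim moves by only 1.5 to 2.8 percentage points over the same range. If control reuse is rare, the effect is negligible. The figures rest on proportional and equal risk, an SD of 0.21 in both arms, 152 analysed per arm and a normal approximation.

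**What to change.** 1. In SAP 4.4.2, add a control-arm crossover exclusion with a numeric threshold, fixed before results by arm are seen. Two candidates are any persistent reuse, following the ban in 4.4.1 and with persistent defined as a count or period, or the mirror image of the 20% rule. The word persistently qualifies the 20% limit in 4.4.1 but not in 4.4.2; the same wording should apply to both arms.
2. In SAP 4.5, define the PP set by reference to 4.4.2, so that one definition remains. A bullet in 4.4.2 alone would leave the two sections in conflict.
3. In SAP 6.1.2, state which set the non-inferiority test uses and what role the PP result has.
4. Record control-arm reuse in the catheter-use questions already asked at scheduled contacts, and report the share of catheterisations with the non-allocated type by arm beside the primary result.

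The cost is a few lines of SAP text, one question in an existing script and a slightly smaller PP set. Excluding control reusers after randomisation may selectively remove frequent catheterisers, so the PP result should be read beside the ITT result and not in its place. For contacts already completed, reuse may not have been recorded in enough detail; if so, the report should say so.
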